## Abstract

**Background:**

The aquatic environment has characteristics that favor adherence to exercise programs among older adults, and studies have shown that programs in this setting are effective in enhancing various aspects of physical fitness, as well as cognitive function, in this population. Research has explored whether incorporating cognitive tasks into an aquatic exercise program could offer additional benefits. Still, it remains uncertain whether this approach leads to greater improvements in cognitive function compared to aquatic exercise alone. We herein report the protocol of the WaterCog Study, which aims to evaluate the effects of an aquatic aerobic exercise program combined with cognitive tasks, compared to a conventional aquatic aerobic exercise program and a control group, on cognitive function and other health-related outcomes in older women.

**Methods:**

This trial is a randomized, single-blinded, three-arm, parallel, superiority trial. A total of 102 older women will be randomized into one of three groups: 1) an aquatic aerobic exercise program combined with cognitive tasks, 2) a conventional aquatic aerobic exercise program, and 3) a control group. Participants in both exercise groups will complete a 12-week exercise program consisting of two non-consecutive sessions per week. The primary outcome is cognitive function, while secondary outcomes include physical function, cardiovascular, and psychosocial parameters. Outcomes will be measured at baseline, post-intervention, and the 12-week follow-up after the end of the intervention period. The analysis plan will employ an intention-to-treat approach and per-protocol criteria.

**Discussion:**

Our conceptual hypothesis is that both aquatic exercise interventions will significantly improve the investigated outcomes compared to the control group. Additionally, we expect that the integration of cognitive tasks will result in additional benefits in cognitive function, cardiovascular outcomes, and psychosocial parameters, with similar gains in physical function compared to conventional aquatic aerobic exercises in post-intervention and follow-up measures. The findings will contribute to the evidence base for interventions targeting cognitive aging and the development of more effective and engaging exercise programs for older adults.

**Trial registration:**

The trial “Aquatic Exercises Combined with Cognitive Tasks for Older Adults (WaterCog)” was prospectively registered at ClinicalTrials.gov (NCT07156708; https://clinicaltrials.gov/study/NCT07156708) in August 2025.

**Supplementary Information:**

The online version contains supplementary material available at 10.1186/s12877-026-07084-8.

## Background

Population aging has intensified worldwide. According to the World Health Organization (WHO), by 2030, one in six people in the world will be aged 60 years or older. At that time, the share of the population aged 60 years and over is expected to increase from 1 billion in 2020 to 1.4 billion. By 2050, the global population of people aged 60 and older is expected to double, reaching 2.1 billion, while the number of individuals aged 80 or older is projected to triple between 2020 and 2050, reaching 426 million [1]. In Brazil, data from the latest Instituto Brasileiro de Geografia e Estatística (IBGE) Census showed that the number of people aged 60 or over grew by 56% between 2010 and 2022 [2]. Although increased life expectancy is an important achievement, the rise in the proportion of older adults leads to higher government spending, particularly on healthcare systems [3].

The aging process generally involves declines in cognitive function, as well as physical, mental, and cardiovascular health, which reduce the independence of older adults. In terms of physical health, reductions in aerobic capacity and muscle strength are evident, negatively affecting functionality and quality of life [4]. Moreover, aging is commonly accompanied by chronic conditions, including mental and cardiovascular disorders, with depressive symptoms and elevated blood pressure being highly prevalent among older adults [1, 5]. Additionally, cognitive aging can negatively affect several domains of cognitive health that are essential for daily functioning, including processing speed, attention, inhibitory control, memory, cognitive flexibility, and semantic fluency [6]. These declines are linked to morphological and functional changes in the brain, particularly in the prefrontal cortex, and are influenced by factors such as cognitive reserve and lifestyle [7]. Although cognitive decline is also a natural process of aging, in some cases it can progress to mild cognitive impairment and even dementia [7]. Emerging evidence suggests that sedentary and unhealthy lifestyles accelerate brain ageing, while regular physical activity, high cardiorespiratory fitness, or a combination of both, can mitigate cognitive impairment and reduce dementia risk [8].

Given this scenario, implementing non-pharmacological strategies that promote healthy aging is essential to address these challenges and mitigate the economic and social impacts of this process [9]. In addition, social isolation and loneliness are public health concerns faced by older adults, as they negatively impact physical and cognitive health [10, 11]. Regular physical exercise plays a key role, as it helps mitigate several deleterious effects of aging and contributes to a healthy aging phenotype [12]. Furthermore, participation in exercise programs increases social interaction, promotes a sense of belonging, and encourages regular engagement in physical activities [13].

In this context, aquatic exercises, typically performed in group settings, have characteristics that favor adherence to exercise programs among older adults. The unique physical properties of water, such as hydrostatic pressure and thermal conductivity, provide benefits in hemodynamic, neuroendocrine, and metabolic parameters [14]. Water immersion has also been shown to increase cerebral blood velocities [15], and aquatic exercise has also exhibited a greater increase in acute cerebral blood flow compared to similar land-based activity in young adults [16, 17]. Furthermore, buoyancy provides a lower impact on lower limb joints [18] and offers a safer environment that minimizes the fear of falling, a widely recognized barrier to exercise participation in this population [19].

It is well established in the literature that aquatic exercise programs are effective in improving multiple components of physical fitness and overall quality of life in older individuals [20–28]. Moreover, aquatic exercise has been shown to promote beneficial effects on blood pressure regulation, contributing to cardiovascular health in older adults [29]. In turn, evidence regarding its influence on sleep quality and mental health outcomes, such as anxiety and depressive symptoms, remains scarce, with only a few studies specifically addressing these aspects among older adults [30, 31]. Recently, its role in cognitive function has also been acknowledged. Aquatic exercise interventions have demonstrated significant improvements in biochemical and physiological biomarkers associated with neuroplasticity and brain health [32, 33]. In addition, significant increases were observed in neuropsychological tests after programs involving different aquatic exercises in older adults [26, 34, 35].

These findings reinforce the potential of aquatic exercise not only in promoting cognitive function but also in exploring interventions that integrate motor and cognitive components. In this scenario, Schaefer et al. [36] evaluated adults under single- and dual-task conditions, combining cognitive and motor tasks, and found significantly fewer errors in the aquatic environment than on land. Regarding chronic adaptations, studies have investigated whether incorporating cognitive tasks into an aquatic exercise program provides additional benefits for older adults. As a result, dual-task aquatic programs have been shown to be effective in improving cognitive function and functional mobility in older adults [37, 38]. In addition, Meekum et al. [39] compared the effects of an aquatic exercise program with and without cognitive training. They found that combining aquatic exercise with cognitive training enhanced cognitive functions more effectively than exercise alone in older adults with mild cognitive impairment. On the other hand, Sato et al. [40], with a similar design but involving participants without cognitive impairment, observed that the group performing aquatic exercise combined with cognitive tasks showed improved cognitive function, whereas the group performing conventional aquatic exercise showed improved physical function. It is noteworthy that the latter studies had methodological limitations regarding the experimental design and exercise programs, which limit the generalizability of the results.

Although the benefits of dual-task aquatic exercise for older adults are promising, it has not yet been proven whether the inclusion of cognitive tasks provides superior gains in cognitive function compared to the same aquatic exercise program alone. On the other hand, the inclusion of cognitive tasks could interfere with gains in physical fitness and associated mechanisms due to limited attentional capacity [41]. Moreover, little is known about how this approach may affect cardiovascular health and psychosocial outcomes, including symptoms of anxiety and depression, sleep quality, and quality of life. Additionally, the latest global consensus on exercise recommendations for older adults emphasizes that multicomponent interventions, which include cognitive tasks, contribute to improving cognition and functional capacity during aging [12]. Thus, interventions involving aquatic exercise programs that provide adaptations in various components of physical fitness, conducted in combination with cognitive tasks, emerge as an innovative strategy, aligned with current recommendations for healthy aging. Therefore, there is a lack of randomized clinical trials with high methodological rigor to clarify these issues, despite the importance of the topic for the health of older adults.

Therefore, we aim to examine the effects of a 12-week aquatic aerobic exercise program combined with cognitive tasks on cognitive function, physical function, cardiovascular, and psychosocial parameters in older women, compared to a conventional aquatic aerobic exercise program and a control group. We hypothesize that both exercise programs will significantly enhance the measured outcomes compared to the control group. Additionally, we expect the aquatic aerobic exercise program with cognitive tasks to have a more pronounced positive effect on cognitive function, as well as on cardiovascular and psychosocial parameters, compared to conventional aquatic aerobic exercise, with similar responses in physical function.

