### Trial design and setting

This trial is a randomized clinical trial employing a 1:1:1 allocation ratio. It was designed as a superiority trial with three parallel groups, and the outcome assessors and data analysis were blinded. This trial is being conducted at the School of Physical Education and Physiotherapy (ESEF) of the Federal University of Pelotas (UFPel), Brazil. The present study protocol was designed in accordance with the SPIRIT Statement 2025 [42].

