### Outcomes

The primary outcome of the study is executive function (verbal fluency subtype), assessed by the Controlled Oral Word Association Test (COWAT; total F-A-S score), which captures aspects of inhibitory control, cognitive flexibility, and verbal initiation. The primary endpoint is the post-intervention time point. The primary analysis will focus on between-group differences at post-intervention, with additional longitudinal analyses examining changes from baseline and the maintenance of effects at follow-up (12 weeks after the end of the intervention).

The secondary outcomes of the study will be presented as group means and include:

Cognitive function, which will be assessed at baseline, post-intervention, and at the 12-week follow-up after the end of the intervention time points:Attention span and short-term memory, measured by the Digit Span Test – Forward (DST–F);Processing speed and visual attention, measured by the Trail Making Test – part A (TMT–A);Executive function (set-shifting ability), measured by the Trail Making Test – part B (TMT–B);Self-perceived cognitive failures, measured by the Cognitive Failures Questionnaire (CFQ).

Physical Function, which will be assessed at baseline and post-intervention time points:Aerobic fitness, measured by the 6-min Walk Test (6MWT);Lower limb strength, measured by performance in the 30-s Chair Stand Test;Upper limb strength, measured by performance in the Arm Curl Test;Lower limb flexibility, measured by the Sit-and-Reach Test (Wells Bench);Agility and dynamic balance, measured by performance in the Timed Up and Go (TUG) Test;Dual-task performance, measured using the TUG combined with a simultaneous cognitive task.

Cardiovascular parameters, which will be assessed at baseline and post-intervention time points:Office blood pressure, measured using a calibrated and automated oscillometric device;Heart rate variability, measured using a heart rate monitor;Blood pressure reactivity, measured using the auscultatory method during the Stroop Test for 3 min;Heart rate reactivity, measured using a heart rate monitor during the Stroop Test for 3 min.

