### Statistical methods

Descriptive data will be presented as means with standard deviations and/or 95% confidence intervals, or as absolute or relative frequencies, when applicable. Generalized Estimating Equations (GEE) will be used to compare primary and secondary outcomes, assuming an unstructured working correlation matrix. In all GEE models, group and time will be treated as categorical variables, and group × time interactions will be included to test intervention effects. Bonferroni-adjusted post hoc tests will be applied when multiple comparisons are performed. The efficacy of the trial will be assessed using a single pre-specified primary outcome and a single primary comparison, consistent with SPIRIT recommendations for clinical trial protocols. Therefore, no multiplicity adjustment across outcomes will be applied. Analyses of secondary outcomes will be considered exploratory, and multiplicity adjustments will be applied only for multiple comparisons within the same outcome (e.g., Bonferroni-adjusted post hoc tests).

Both per-protocol (PP) and intention-to-treat (ITT) analyses will be conducted. In the analysis following the ITT principle, all randomized participants are analyzed in the group to which they were initially assigned, regardless of adherence, treatment receipt, or protocol deviations. Multiple imputations will be used to impute missing data using a specific function on SPSS software. Additionally, PP analyses will be performed to evaluate the robustness of the findings and the effect of adherence to the intervention. Therefore, participants must have at least 70% attendance during the 12-week intervention to be included in the PP analysis. This threshold was defined to ensure sufficient exposure to the training stimulus to plausibly induce adaptations, while accounting for the variability in attendance commonly observed in exercise interventions involving older adults. This cutoff has been adopted in previous aquatic exercise intervention studies conducted by our research group involving older populations under similar conditions [22].

No additional analyses, such as subgroup or sensitivity analyses, are planned for this trial. All statistical procedures will be performed in the SPSS vs. 28.0 program, and the significance level adopted is α = 0.05. Additionally, between-group effect sizes will be calculated using Cohen's d based on change scores and classified as small (≥ 0.2), moderate (≥ 0.5), or large (≥ 0.8) [60, 61].

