On the other hand, gains in physical parameters are expected to be similar in both training groups. Regarding the proposed exercise programs, it is noteworthy that aerobic training programs lasting between 12 and 16 weeks can induce multicomponent adaptations [20–25] due to the multidirectional resistance offered by water. Therefore, the programs were designed to ensure that the physical component was equivalent across both training groups, with the group receiving cognitive tasks being exposed to an additional intervention, allowing any possible differences between the groups to be attributed to this condition. Based on the theory of parallel processing, which states that the central nervous system can process different types of information (e.g., motor and cognitive) simultaneously, but within a limited attentional capacity [41], it is possible that overlapping demands might not only result in similar physical gains but could even lead to reduced physical performance in the dual-task group. To mitigate this potential interference, cognitive tasks were deliberately introduced during active recovery periods, when physical effort levels were lower. This strategy was adopted to reduce competition for attentional resources during phases of higher physical demand, thereby preserving the primary aerobic training stimulus. During active recovery, participants remain physically engaged at a lower intensity, which allows the integration of cognitive challenges without compromising the execution and safety of movements.

The aquatic aerobic exercise program combined with cognitive tasks represents a relatively emerging approach in the aquatic exercise setting, as previous studies have provided limited detail on the structure and dosage of cognitive-motor training in this environment [37–40]. Dual-task approaches combining aerobic exercise and cognitive load have also been described within brain endurance training (BET) frameworks, which typically involve sustained cognitive demands aimed at inducing mental fatigue [70, 71]. Evidence from studies in healthy young adults suggests that continuous dual-task interventions may induce acute cognitive fatigue when sustained for prolonged periods [72, 73]. Although it remains unclear whether similar effects occur in older adults, particularly in the aquatic environment, cognitive fatigue may influence safety, task performance, and adherence, which justifies the dosage proposed in the present study.

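### Similar physical-function gains are hypothesised, also at follow-up, but physical function is not measured at follow-up and the planned difference tests cannot support a conclusion of similarity

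*Protocol article*

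**What the plan says.** **Hypothesis.** The last paragraph of the Background expects the combined programme to be better on cognitive, cardiovascular and psychosocial outcomes "compared to conventional aquatic aerobic exercise, with similar responses in physical function". The Discussion paragraph of the Abstract adds time points: "with similar gains in physical function compared to conventional aquatic aerobic exercises in post-intervention and follow-up measures". The main Discussion repeats that "gains in physical parameters are expected to be similar in both training groups", and also allows that overlapping demands "could even lead to reduced physical performance in the dual-task group".

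**Design and analysis.** Under Trial design and setting: "It was designed as a superiority trial with three parallel groups". Under Statistical methods, the model is a GEE in which "group × time interactions will be included to test intervention effects", followed by Bonferroni-adjusted post hoc tests at α = 0.05 and Cohen's d on change scores. Secondary outcomes are called exploratory, and no additional analyses are planned. The section Protocol and statistical analysis plan says that the analysis plan is contained in this article.

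**Measurement.** Under Outcomes: "Physical Function, which will be assessed at baseline and post-intervention time points". Cardiovascular and psychosocial parameters have the same two time points. By contrast: "Cognitive function, which will be assessed at baseline, post-intervention, and at the 12-week follow-up after the end of the intervention time points". Table 3 agrees: at T5 only COWAT, DST-F, TMT and self-perceived cognitive function are marked.

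**The concern.** There are two separate problems.

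1. The Abstract predicts results at a visit where three of the four outcome domains are not assessed. No analysis can address that part.
2. Similarity of physical gains matters to the trial's argument. The Background and Discussion name interference from the cognitive tasks as a possible cost, and the tasks were placed in the recovery intervals to avoid it. Whether that worked is a real question, but a test built to detect a difference cannot answer it with a yes. A non-significant result is compatible both with no loss and with a material loss, and it becomes more likely as the trial gets smaller or noisier.

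At stake is whether the trial may say that adding cognitive tasks leaves fitness gains intact.

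**Working it through.** **A. Time points side by side**

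| Domain | Abstract hypothesis | Outcomes and Table 3 |
|---|---|---|
| Cognitive | post-intervention and follow-up | baseline, post-intervention, follow-up |
| Physical | post-intervention and follow-up | baseline, post-intervention |
| Cardiovascular | post-intervention and follow-up | baseline, post-intervention |
| Psychosocial | post-intervention and follow-up | baseline, post-intervention |

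The last three rows do not match.

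**B. The plan's own sample size.** Sample size gives f = 0.180, power 90%, α = 5%, N = 84, raised to 102. For a repeated-measures interaction with 3 groups and 3 times, and correlation 0.5 and sphericity assumed (neither is stated), λ = 0.18² × 84 × 3 / (1 − 0.5) = 16.33 on 4 and 162 degrees of freedom. Power is 0.909, so 84 reproduces. Adding 20% gives 84 × 1.2 = 100.8, or 102 in three equal arms. That is 34 per arm randomised and 84/3 = 28 per arm before the dropout allowance. The size was set for a difference in COWAT, not for similarity of fitness.

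**C. What a two-arm difference test can show for physical function.** Work in SD units with n per arm. The standard error is SE = k × √(2/n), where k reflects the use of baseline:

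- post-intervention values only: k = 1
- change score: k = √(2(1 − r)), which is 1 at r = 0.5 and √0.6 = 0.775 at r = 0.7
- baseline-adjusted: k = √(1 − r²) = √0.51 = 0.714 at r = 0.7

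The baseline correlation r is an assumption; the protocol gives none. At n = 34, √(2/34) = 0.2425. The chance of a non-significant result comes from the noncentral t with 66 degrees of freedom and noncentrality d/SE. Figures in brackets use α = 0.05/3.

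| n = 34 per arm | SE | d/SE at d = 0.5 | Non-significant, true loss 0.5 SD | Non-significant, true loss 0.3 SD | 95% CI half-width |
|---|---|---|---|---|---|
| k = 1 | 0.243 | 2.06 | 47% (65%) | 77% (88%) | 0.48 SD |
| change score, r = 0.7 | 0.188 | 2.66 | 25% (42%) | 65% (80%) | 0.38 SD |
| baseline-adjusted, r = 0.7 | 0.173 | 2.89 | 19% (33%) | 60% (76%) | 0.35 SD |

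The half-width is t(0.975; 66) × SE, for example 1.997 × 0.2425 = 0.48. At 28 per arm the 0.5 SD column becomes 55% (72%), 34% (52%) and 27% (44%).

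**D. What a margin rule could show at this size.** The protocol states no margin, so ±0.5 and ±0.3 SD are assumed for illustration. If the true difference is 0, the chance that the 95% CI lies inside ±M is about 2Φ(M/SE − 1.96) − 1, floored at 0.

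- M = 0.5, k = 1: 2Φ(2.06 − 1.96) − 1 ≈ 8%. With the conventional equivalence test (90% CI) it is 32%.
- M = 0.5, baseline-adjusted, r = 0.7: 2Φ(2.89 − 1.96) − 1 ≈ 65%.
- M = 0.3: essentially 0% in every row, because the half-width already exceeds 0.3 SD.

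**The case against.** A reader might infer that the trial will declare similarity whenever p > 0.05. The documents do not support that. No section states such a rule, the wording is that of an expectation, and the Discussion openly allows the opposite result.

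Physical function is also secondary and declared exploratory, and the superiority label and sample size belong to COWAT. A superiority trial may voice an expectation about an exploratory outcome without a formal equivalence test. Cohen's d with size classes is planned, so the reader would see more than a p-value.

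It would likewise be too strong to say that the planned test misses a 0.5 SD loss about half the time. That figure holds for post-intervention values alone, or for a change score at correlation 0.5. At correlation 0.7 it falls to 25% for a change score and 19% with baseline adjustment.

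Finally, the follow-up wording for physical function occurs in one sentence of the Abstract. The Background and main Discussion do not claim follow-up effects for it.

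All of this lowers the severity. It does not remove the mismatch in time points. Nor does it supply what a conclusion of similarity needs: a confidence interval for the between-arm difference is not explicitly promised, and no margin is given. Because the article says that it contains the analysis plan, these cannot be presumed to lie elsewhere.

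**Conclusion.** The point holds in two limited parts.

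1. The Abstract's follow-up hypothesis for physical, cardiovascular and psychosocial outcomes contradicts the assessment schedule and cannot be tested. This rests on the text alone.
2. The planned difference tests and Cohen's d cannot support a conclusion that physical gains are similar in the two exercise arms. At 34 per arm, a true 0.5 SD loss would go undetected in 19–47% of trials (33–65% with Bonferroni for three pairs), and a 0.3 SD loss in 60–77% (76–88%). The 95% CI half-width is 0.35–0.48 SD. These ranges assume full retention, a common SD and a baseline correlation that the protocol does not state. The reasoning itself does not depend on them.

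Severity is minor to moderate: the outcomes are exploratory and the primary COWAT analysis is unaffected.

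**What to change.** - **Follow-up:** limit the follow-up hypothesis in the Abstract to the cognitive outcomes measured at T5.
- **Reporting:** for physical function at post-intervention, report the combined-minus-conventional difference with its baseline-adjusted 95% CI, and state that a non-significant difference will not be read as similarity.
- **Claim:** call the gains similar only if that CI lies within a margin fixed before analysis for a named test, such as the 6MWT. Otherwise call the result inconclusive, or reword the expectation as descriptive from the start.

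**Cost:** some wording and, if the claim is kept, one justified margin. No new data are needed, and with recruitment expected to run to August 2027 the change can be recorded before analysis. The downside is that, for margins of about 0.5 SD or less, the similarity question will probably end as inconclusive unless the baseline correlation is high. If no margin can be justified, the descriptive wording is the proportionate choice.
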